### Blinding

Blinding will not be feasible in this trial, but the physicians of participants randomised to the control group will not be communicated about their patients’ participation in the trial. This is necessary to limit the potential influence on the physician to start statin therapy in control subjects. It is still possible that some control group participants start actively seeking statin therapy from their physician or elsewhere. However, we assume that the proportion of these active individuals will not be high and will not modify the overall study outcomes.

### Data collection methods

All study participant data are collected and stored in the REDCap database, with a dedicated data collection form completed for each participant at every study visit.^28^ Data stored in REDCap includes information from study visits, telemedicine appointments, safety reporting, participant online surveys.

An overview of data collection methods for both study arms is provided in online supplemental table S1.

### Data management

All trial-relevant documentation is stored electronically in an electronic Trial Master File.

Personal data will remain confidential for the duration of the study as pseudonymisation will be performed by allocating number codes to each trial participant in the study database. The pseudonymisation key will be stored on the EstBB’s restricted access server, which is not connected to the internet. The data stored in REDCap and the code key will be destroyed after 25 years after the end of the study. The health data collected during the study will be added to the EstBB database and stored there indefinitely in accordance with §18 of the Human Genome Research Act.

### Statistical methods

The primary analysis includes all randomised participants, regardless of intervention compliance, according to the group to which they were assigned from the time of randomisation until the occurrence of the primary composite outcome (time to MACE), based on the treatment policy estimand strategy (intention-to-treat principle). The outcomes for individuals reaching the end of the study without an observed MACE or dying due to another cause will be censored in the primary analysis.

All statistical tests will be two-sided, the level of statistical significance (α) will be 5%, and 95% CIs will be used. Statistical analyses of secondary endpoints will not be formally adjusted for multiplicity. Therefore, these results will be interpreted as exploratory. The statistical analysis will be described a priori in a statistical analysis plan.

Each study subject will be followed for a minimum of 5 years. The primary outcome will be evaluated through a registry-based analysis in both the study and control arm. The trial’s endpoint adjudication committee will assess and confirm the validity of all events.

Crude incidence rates per 1000 person-years will be reported as the number of subjects with events over 5 years divided by the total time at risk for the intervention group of interest (study arm/control arm). For subjects with events, the time at risk will be the time of the first event. For subjects without events, it will be the end of the trial, the time of death (without experiencing the event), or withdrawal of the consent.

The intervention effect is measured by the adjusted HR calculated with 95% CIs, using the Cox proportional hazards model adjusted for gender and age. As 5 years is not a long follow-up period, we might not be able to detect departures from proportionality. However, in case the departures are still detected, stratified log-rank tests will be used instead.

Interim analyses will not be conducted by the research team. An independent Data Monitoring Committee (DMC) will periodically review accumulating efficacy and safety data.

After the clinical trial concludes, a 3-year additional follow-up period will start. At the end of this period, an analysis of registry data concerning the primary endpoint (MACE outcomes) will be conducted. Details about the secondary outcome analyses, subgroup analyses, cost–utility analysis and substudies (microbiome and pharmacogenetics) are provided in the full study protocol.

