### Sample size and power calculation

The power calculations are based on the EstBB cohort, accounting for the observed age and risk factor distribution and the estimated effect sizes. The sampling frame is based on all EstBB gene donors (211 739 individuals).^24 25^ The CAD PRS have been previously calculated for all participants based on the method described by Patel *et al*.^26^

The study target sample includes men aged 45–80 years and women aged 55–80 years who are within the top 20% CAD PRS. The sample used for modelling (n=36 405, 17 861 men, 18 544 women) satisfied the following criteria:

No prevalent CVD (as defined in the protocol), no missing values in body mass index, systolic blood pressure, smoking level and PRS;Age 45–80 at agreement for men and 55–80 for women.

The actual EstBB cohort was used for sample size calculation, assuming that the study sample will be a random sample from all eligible participants. The potential outcome distributions were obtained based on statistical simulation, assuming that the age-specific 5-year major adverse cardiovascular event (MACE) incidence without statin treatment will be similar to what has been observed in the cohort (the Weibull distribution appeared to provide an appropriate approximation) and that the statin treatment will reduce the outcome hazard up to 30%.

Based on an anticipated hazard reduction of 30% with statin treatment and allowing for up to 10% dropout, a recruitment target of 2700 participants is set to ensure a minimum of 80% statistical power.

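### The primary Cox model adjusts only for gender and age; adding pre-randomisation biobank predictors would recover a small amount of power at little cost

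*Protocol article*

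**What the plan says.** Under Statistical methods, the protocol article fixes the primary effect measure as an HR estimated "using the Cox proportional hazards model adjusted for gender and age", and gives no reason for stopping at two covariates. Tests are two-sided at 5%.

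Under Sample size and power calculation it states that "The CAD PRS have been previously calculated for all participants". It describes a modelling sample restricted to donors with "no missing values in body mass index, systolic blood pressure, smoking level and PRS", and says that the calculation took account of the distribution of age and risk factors. The design is "Based on an anticipated hazard reduction of 30% with statin treatment" and "allowing for up to 10% dropout"; on that basis "a recruitment target of 2700 participants is set" "to ensure a minimum of 80% statistical power".

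Under Randomisation, allocation is automatic once consent is signed. The trial's own baseline measurements follow: with the family physician in the intervention arm (Intervention arm section), and at partner hospitals and laboratories in the control arm (Control arm section).

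**The concern.** Smoking, blood pressure, body mass index and the PRS would be expected to predict cardiovascular events beyond age and sex. The sponsor judged them relevant enough to require complete values in the power modelling. Values recorded before randomisation are legitimate covariates and need no new data.

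In a Cox model, omitting a predictor of outcome moves the estimated HR towards 1 even when randomisation has balanced it. The stated target is a minimum of 80% power, and the article itself acknowledges that control participants who know their PRS may seek statins, which would dilute the effect. Power that can be had by pre-specifying covariates is therefore worth considering.

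**Working it through.** **1. The plan's own figure.** Inputs from the article: HR 0.70, two-sided 5%, 80% power, 1:1 allocation, 2700 recruited, 10% dropout.

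- Schoenfeld: 4 × (1.960 + 0.842)² / (ln 0.70)² = 4 × 7.849 / 0.1272, giving 247 events.
- Freedman: 7.849 × (1.70 / 0.30)² = 7.849 × 32.11, giving 253 events.
- Evaluable: 2700 × 0.90 = 2430.
- Implied control 5-year risk p, from (2430/2) × [p + 1 − (1 − p)^0.70] = events: 11.9% for 247 events and 12.2% for 253. With all 2700 evaluable it is 10.7% to 10.9%.

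The article gives no event rate or event count, so 2700 cannot be reproduced. The 11.9% used below is back-solved and is an assumption.

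**2. How much extra prognostic spread is plausible.** The article gives no predictor effects. Assumed: smoking HR 1.9 at 20% prevalence, blood pressure 1.25 per SD, body mass index 1.15 per SD, PRS 1.5 per population SD. Contributions to the variance of the log-hazard:

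- Smoking: 0.642² × 0.2 × 0.8 = 0.066
- Blood pressure: 0.223² = 0.050
- Body mass index: 0.140² = 0.020
- PRS over its full range: 0.405² = 0.164
- PRS within the top 20%, if roughly normal (SD 0.47 of the population SD): 0.164 × 0.47² = 0.036

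The combined SD is √0.300 = 0.55 if the PRS range is ignored, but √0.172 = 0.41 for the population actually enrolled. Effects 1.5 times as strong on the log scale give 1.5 × 0.41 = 0.62.

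**3. Simulation.** 2000 trials per row, 2430 participants, control risk 11.9%, conditional HR 0.70. Assumed log-HR 0.07 per year of age and 0.6 for men. The extra predictors are complete and combined into one term with the SD shown.

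| SD of extra log-hazard | Mean HR: age+sex → full | SE of log-HR: age+sex → full | Power %: age+sex → full | Gain (points) |
|---|---|---|---|---|
| 0.2 | 0.701 → 0.700 | 0.1290 → 0.1290 | 78.50 → 79.25 | 0.75 |
| 0.4 | 0.700 → 0.697 | 0.1291 → 0.1292 | 78.25 → 78.75 | 0.50 |
| 0.6 | 0.705 → 0.698 | 0.1286 → 0.1287 | 77.20 → 79.70 | 2.50 |
| 0.8 | 0.714 → 0.700 | 0.1285 → 0.1286 | 75.65 → 80.60 | 4.95 |
| 1.0 | 0.718 → 0.696 | 0.1280 → 0.1282 | 73.95 → 80.45 | 6.50 |

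**4. Mechanism.** Power is approximately Φ(|log-HR| / SE − 1.96). At SD 0.6 this is Φ(0.3496/0.1286 − 1.96) = Φ(0.758) = 77.6% with age and sex, and Φ(0.3598/0.1287 − 1.96) = Φ(0.836) = 79.8% with the extra term. The SE does not fall; the whole gain comes from the log-HR.

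**5. Placing this trial.** Modest effects with the PRS confined to its top 20% (SD 0.41) correspond to the second row. Runs with the four covariates entered by name gave gains of 1.0 point (simulation error 0.4) and 0.8 points (78.0% to 78.8%). Taken together, the gain is about 1 point, close to simulation error. For effects 1.5 times as strong (SD 0.62), the third row gives 2.5 points and a run with the named covariates about 4. At a true HR of 0.75 with modest effects, power goes from 62.5% to 63.1%. The PRS alone adds almost nothing within its restricted range.

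**The case against.** The strongest objection is that a pre-specified Cox model with gender and age is sound, and that a longer covariate list is a preference. That the model is sound stands: this is neither an error nor a contradiction. Several stronger readings are tempting, and the documents do not support them.

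- *Precision is lost.* A reader might expect adjustment to narrow the confidence interval. For a Cox log-HR it does not, as the SE column shows.
- *The gain is entirely free.* The complete-case restriction suggests that some donors lack values, no missingness rate is given, and the eligibility box does not require these measurements. They may be years old. The simulations assume complete, current values, so they are upper-end for the effects assumed.
- *The analysis contradicts the power model.* The article names the four variables only as a completeness criterion and says that risk factor distributions were considered. It lists no simulation terms, and the one incidence input it describes is age-specific. An analysis model also need not match the model used to simulate outcomes.
- *There is no slack.* The article promises at least 80% and gives no event rate. The 11.9% risk was solved to give about 80%, so it cannot show that slack is absent.
- *Gains of 5 points or more.* These need a combined SD of 0.8 or above, roughly twice the modest effects, and the document offers nothing to support that.

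One might also say that covariates belong in the statistical analysis plan. But the article itself fixes the primary covariate set, so the choice is open to comment.

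**Conclusion.** The point holds as a low-severity efficiency suggestion. The primary model is valid but leaves out predictors that exist before randomisation, and so forgoes a small amount of power through a slight pull of the HR towards 1. The gain is about 1 power point for modest predictors and up to about 4 for stronger ones. This rests on assumed predictor effects, a 20% smoking prevalence, an approximately normal PRS cut at its top 20%, a back-solved control risk of 11.9%, and complete biobank values. Stale or missing values would lower it. No run showed a credible loss of power.

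**What to change.** Before any outcome data by arm are seen, pre-specify the primary Cox model with:

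- sex, continuous age and continuous PRS;
- the biobank (pre-randomisation) values of smoking, systolic blood pressure and body mass index;
- a stated rule for missing values, such as simple imputation or a missing indicator.

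State that study-visit baseline values are not used as covariates, since they are taken after allocation and in different settings by arm. Keep the gender-and-age model as a sensitivity analysis.

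The cost is a sentence or two of text, a check of biobank completeness, and the missing-value rule. It needs no new data, visits or participants. The downside is that the HR becomes conditional on more covariates and so differs slightly from the gender-and-age HR; the report should say so.

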## Methods

### Trial design

This is a pragmatic, multicentre, open-label, parallel group, randomised clinical trial with a 1:1 allocation ratio to intervention (n=1350), receiving preventive rosuvastatin 20 mg treatment or control (n=1350), receiving current standard of care.

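### If proportional hazards fail, the plan replaces the adjusted hazard ratio with stratified log-rank tests, which do not cure a non-proportional treatment effect and leave no between-arm effect estimate

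*Protocol article*

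**What the plan says.** All of this is in the Statistical methods section of the protocol article.

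- Effect measure: "The intervention effect is measured by the adjusted HR calculated with 95% CIs, using the Cox proportional hazards model adjusted for gender and age".
- Expected ability to find a violation: "As 5 years is not a long follow-up period, we might not be able to detect departures from proportionality".
- Rule if one is found: "in case the departures are still detected, stratified log-rank tests will be used instead".
- General rule: "All statistical tests will be two-sided, the level of statistical significance (α) will be 5%, and 95% CIs will be used".

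The only other summary of the primary outcome is a crude event rate per 1000 person-years in each arm. No difference or ratio of these rates, and no interval for one, is defined. The section does not say whether the departure it has in mind concerns treatment or one of the two covariates.

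**The concern.** The rule substitutes one analysis for another; it does not add one. Three things follow.

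1. The replacement should address the problem that triggers it. A log-rank test uses the event weighting that is optimal under proportional hazards, which is also the Cox weighting.
2. A log-rank test gives a p-value. When the rule fires, the HR and CI that the same section promises disappear for the primary outcome, and nothing is named in their place. An effectiveness trial needs a magnitude, most of all when the effect changes over time.
3. Whether an effect estimate is reported depends on a check of the trial's own outcome data, and the authors expect that check to be weak.

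This is a rule stated in the article, not a detail left open. An analysis plan that followed it would carry the same fault.

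**Working it through.** **1. The plan's own figure.** Inputs from Sample size and power calculation: "Based on an anticipated hazard reduction of 30% with statin treatment" (HR 0.70), and "allowing for up to 10% dropout, a recruitment target of 2700 participants is set to ensure a minimum of 80% statistical power". Allocation is 1:1 and alpha is 5% two-sided.

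- Schoenfeld: 4 × (1.960 + 0.842)² / (ln 0.70)² = 4 × 7.849 / 0.1272 = 246.8, so 247 events.
- Freedman: 7.849 × (1.70 / 0.30)² = 252.04, so 253 events.
- Dropout: 2700 × 0.9 = 2430 evaluable, 1215 per arm.

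The article gives no control event rate, so 2700 cannot be reproduced outright. Solving 2430 × [p + 1 − (1 − p)^0.7] / 2 = 247 or 253 gives an implied control 5-year risk p of 11.9% or 12.2% (10.7% or 11.0% if all 2700 count). I therefore **assume** about 12%. That gives 250 events and 80.5% power. Over assumed risks of 8% to 16%, power runs from 63% (166 events) to 90% (334 events). The sample size is not in dispute; this step only sets the scale for the simulations.

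**2. Why the two tests coincide.** At each event, let A be 1 if the event is in the intervention arm and 0 otherwise, and let p be the intervention arm's share of those at risk. The log-rank statistic is Z = Σ(A − p) / √Σp(1 − p), with weight 1 on every event. With no tied event times, that is the Cox partial-likelihood score test at HR = 1. Summing within strata gives the score test of the stratified Cox model. This is structural and does not depend on the assumed 12%.

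**3. Simulation without covariates or strata.** 3000 trials per scenario, 1215 per arm, exponential control risk of 12% at 5 years. Rejection rates (%):

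| True treatment effect | Log-rank | Cox Wald | Late-weighted, FH(0,1) | 5-year RMST |
|---|---|---|---|---|
| None | 4.6 | 4.5 | 6.1 | 4.4 |
| HR 0.70 throughout | 79.4 | 79.2 | 67.4 | 67.9 |
| None for 1 year, then 0.62 | 81.1 | 80.9 | 85.3 | 50.0 |
| None for 2 years, then 0.50 | 78.8 | 78.6 | 94.4 | 28.2 |
| 0.50 to 2.5 years, then 0.90 | 81.7 | 81.6 | 33.0 | 93.5 |
| 1.4 to 2 years, then 0.6 | 9.2 | 9.2 | 54.1 | 13.2 |

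Log-rank and Cox gave the same decision in at least 99.8% of trials in every row, with a Z correlation of at least 0.9999.

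**4. Simulation closer to the plan.** 1200 trials, N = 2430, assumed control risk 11.9%, with age, sex and one further prognostic factor. The Cox model was adjusted for age and sex; the log-rank test was stratified by sex and four age bands.

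| True effect | Adjusted Cox | Stratified log-rank | 5-year risk difference |
|---|---|---|---|
| None for 1 year, then 0.62 | 74.5% | 74.8% | 75.2% |
| None for 2 years, then 0.55 | 65.7% | 65.9% | 68.2% |

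Cox and log-rank agreed in 98.5% of trials (Z correlation 0.996). The risk difference was about 3 percentage points. The Monte Carlo standard error is about √(0.745 × 0.255 / 1200) = 1.3 points, so I claim no power advantage for it. Power levels differ between steps 3 and 4 because the models differ; only comparisons within a table matter.

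**5. Does switching inflate type I error?** 4000 null trials, N = 2430, assumed 12% risk, age, sex and one further factor, with a proportionality pre-test at 5%: rejection was 4.8% for Cox, 5.0% for stratified log-rank and 4.8% for the switching rule. No inflation is visible.

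**6. What is left after the switch.** Before: HR, 95% CI, test, and a crude rate per arm. After: test, and a crude rate per arm. The decision hardly moves; the estimate is lost.

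**The case against.** The strongest reply is that the harm is narrow. The log-rank test needs no proportional hazards to be valid under the null. If it agrees with Cox in nearly every trial, choosing between them can hardly change the conclusion, and the null simulation bears this out. All of that stands. It limits the point to the missing estimate and to reporting that depends on a weak check.

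Second, the departure may concern age or gender, and stratifying on such a factor is a standard repair. That also stands. But a stratified Cox model makes the same repair and keeps the HR, so it does not justify replacing the estimate with a test.

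Third, per-arm rates are reported in any case, so the effect is not wholly unquantified. True, and a rate ratio or difference could be formed from them, but the article defines neither a contrast nor an interval.

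Some stronger readings are tempting and are not supported:

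- A reader might infer that the switch costs power, or that deleting it would gain some. It does neither, because the test is practically the same.
- A reader might infer that there are no randomisation strata to stratify by. The Randomisation section mentions permuted blocks and is silent on strata; silence in a condensed article is not evidence. A stratified log-rank test does not need randomisation strata anyway, and age bands are ordinary analysis-plan detail.
- A reader might infer that any measure free of proportional hazards would do equally well. RMST had only 50.0% and 28.2% power under the two delayed-benefit patterns in step 3.

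**Conclusion.** The point holds as a badly fixed rule; severity should-fix. For a non-proportional treatment effect, the fallback repeats essentially the same test (agreement 98.5% with covariates and strata, at least 99.8% without) and gives up the HR and CI with no named replacement. That conflicts with the section's own statements that the effect is measured by an HR and that 95% CIs will be used. It bites only if a departure is detected. Type I error is not harmed, and the significance decision would rarely change.

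The simulated figures rest on an assumed control risk near 12% and on chosen effect shapes; they are illustrative. The equivalence of the tests and the loss of the estimate do not depend on them.

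**What to change.** Delete the switch and state instead:

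- The adjusted Cox HR, its 95% CI and its test remain the primary analysis whatever the proportionality check shows. If the treatment effect is non-proportional, the HR is read as an average over the 5 years.
- If age or gender is the non-proportional term, the Cox model is stratified on it, so that the HR and CI are kept.
- The between-arm difference in 5-year cumulative incidence of MACE, with 95% CI, is always reported as a supportive measure that does not need proportional hazards.

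The cost is one sentence in the protocol or analysis plan and one table row. The sample size is unchanged, and no power is gained or lost because the primary test stays the same. The change should be made before outcome data are analysed, so that it cannot look data-driven.

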### Clinical endpoint adjudication committee

A Clinical Endpoint Adjudication Committee (CEAC) has been established given the composite nature of the primary endpoint, which requires independent expert review to confirm the validity of all qualifying events. The CEAC comprises three independent cardiologists who conduct annual assessments, blinded to treatment allocation, of primary endpoints identified through registry queries and electronic health records (EHR), adjudicating each event against predefined trial endpoint criteria. CEAC members are bound by strict confidentiality obligations and are prohibited from disclosing any trial-related information to parties outside the committee, including the principal investigator.

### Data monitoring committee

The DMC is an independent multidisciplinary team comprising a biostatistician, a cardiologist and a primary care specialist. The DMC monitors participant safety and data integrity throughout the trial. The operational details of DMC activities will be described in the DMC Charter prior to the start of DMC work.

### Trial monitoring

Study monitoring independent from study team will be performed according to International Council for Harmonisation Good Clinical Practice guidance version E6(R3) by the Clinical Research Centre of the Tartu University Hospital. Monitoring will be performed according to the approved monitoring plan. Mainly central monitoring will be used, if needed, site visits can be performed. Central monitoring includes the monthly monitoring of protocol deviations based on REDCap reports. By the end of each month, a summary of the monitoring results will be provided to the study coordinator. Any identified discrepancies must be resolved within 1 month and are monitored until full resolution.

